### Sample size

According to the study objective and previous study results [32] with α = 0.01, β = 0.1, p_1_ = 0.51 and p_2_ = 0.021, the sample size will be *n* = 23. Considering a 20% dropout rate, the final sample size will be 58 women (29 women in each group).$$\begin{array}{l}n=\frac{{\left({z}_{1-\alpha /2}+{z}_{1-\beta }\right)}^{2}*\left[{p}_{1}\left(1-{p}_{1}\right)+{p}_{2}\left(1-{p}_{2}\right)\right]}{\left({p}_{1-}{p}_{2}\right)^{2}}\\ \mathrm{Z}_{1-\mathrm{\alpha }/2}=2.57\\ \begin{array}{l}\mathrm{Z}_{1-{\mathrm\upbeta} }=1.28\\ {\left(2.57+1.28\right)}^{2}*\left(0.55\left(0.45\right)+0.021\left(0.979\right)\right)/{\left(0.529\right)}^{2}=23\end{array}\end{array}$$

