### Data collection

This phase of the randomized clinical trial will be conducted with the participation of 58 undergraduate midwifery students at their 7th and 8th semesters. The students will be divided randomly to intervention (continuous care) and control (routine care) groups providing care to 58 pregnant women in six health centers and two hospitals (Sina and Razi) in Ahvaz city, southwest of Iran.

The study will begin after receiving the approval of the Ethics Committee of Ahvaz University of Medical Sciences and registering the study in the Iranian Registry for Randomized Clinical Trials. Inclusion criteria will be willingness to participate in the study.

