### Randomization

To implement the intervention, the students will be divided into two intervention (providing continuous care for pregnant women) and control (providing standard care for pregnant women) groups. Allocating students will be done using permuted block randomization technique with a block size of four and an allocation ratio of 1:1. Five blocks of 4 pieces and 3 blocks of 3 pieces will be extracted randomly using WIN PEPI software. In each block of 4, 2 students will be in control and 2 will be in intervention group. Also, in each block of 3 students, 1 student will be in control and 2 will be in intervention group, and the arrangement of each person is random. To prevent contamination, first the control group will provide routine care, and then the intervention group will conduct continuity of care for pregnant women. Mothers are randomly selected based on the hospital where they will give birth. As a result, Razi Hospital will be the control group and Sina Hospital will be the intervention group.

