### Intervention

Women who meet the inclusion criteria will be recruited in the study using a non-probability convenience sampling method. Women in the intervention group will be included in the study after their first pregnancy visit (6–10 weeks of gestation) and will receive continuous care by midwifery students. Women in the control group will receive the usual and routine care, and will be included in the study at the time of delivery. They will have a gestational age of more than 37 weeks based on the inclusion criteria of the study. Their delivery will be performed by midwifery students who will follow them up until six weeks after delivery.

At first, the necessary training will be given by the lead researcher (FR) to the students in orientation sessions held for both groups separately. In the intervention group, each midwifery student as the main midwife will be responsible for taking care of two or three pregnant women and will be the back-up midwife for two other pregnant women (under the supervision of other students). The lead researcher will create a group in WhatsApp with the participation of students in the intervention group, and they can communicate with each other and the researcher. Also, the midwifery students will be directly and indirectly under the supervision of a qualified person (lead researcher). Another WhatsApp group will be created for the women of the intervention and control groups (to facilitate communication between the researcher and the women). Two midwifery students will be introduced to each pregnant woman in the intervention group (as a main midwife and a backup midwife). If the main midwife is not available, the woman will be in contact with the backup midwife. The backup student will meet the woman at least once and will be introduced to her.

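### The listed blocks allocate 29 students at 16:13, against 58 students, a block size of four and a 1:1 ratio stated elsewhere in the plan

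*Protocol article*

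**What the plan says.** Four statements in the protocol article bear on how many students are allocated, and how.

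- **Number of students.** The Data collection section of the quantitative phase describes a trial "with the participation of 58 undergraduate midwifery students at their 7th and 8th semesters" and adds: "The students will be divided randomly to intervention (continuous care) and control (routine care) groups".
- **Method.** The Randomization section names permuted blocks "with a block size of four and an allocation ratio of 1:1".
- **Block list.** The same section continues: "Five blocks of 4 pieces and 3 blocks of 3 pieces will be extracted randomly using WIN PEPI software". Blocks of four hold two control and two intervention students. For the others, "in each block of 3 students, 1 student will be in control and 2 will be in intervention group".
- **Women.** The Sample size section concludes that "the final sample size will be 58 women (29 women in each group"). The Intervention section says that, in the intervention group, "each midwifery student as the main midwife will be responsible for taking care of two or three pregnant women".

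The Primary outcome section names the clinical competence of the students. The Sample size section compares two proportions and sizes the groups of women. No calculation is given for students.

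**The concern.** The block list is stated in full, so it can be added up, and it does not give the number of students or the ratio that the plan states. Blocks of three also depart from the stated block size and cannot be split evenly.

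This goes beyond wording because the student is the unit of the primary outcome. With no sample size calculation for students, the figure of 58 in the Data collection section is the only direct statement of the primary sample, and the block list implies half of it. A reader cannot tell how many students will be compared. An allocation that follows the list cannot also satisfy the rest of the paragraph.

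**Working it through.** **1. Total and split of the list** (inputs from the Randomization section)

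- Total: 5 × 4 + 3 × 3 = 20 + 9 = 29
- Intervention: 5 × 2 + 3 × 2 = 10 + 6 = 16
- Control: 5 × 2 + 3 × 1 = 10 + 3 = 13
- Ratio: 16/13 = 1.23 to 1, with 55.2% in the intervention group

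The stated figures are 58 students at 1:1, that is 29:29. Neither the number nor the ratio is reproduced.

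**2. Can another reading recover 58 at 1:1?**

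- *List used twice* (for example, once per semester): 58 students, 32 intervention and 26 control. The number is right, the ratio is not.
- *Another count of the same two block types*: with *a* blocks of four and *b* blocks of three, 4*a* + 3*b* = 58, and the intervention group exceeds control by *b*. Equality needs *b* = 0, but 58 is not a multiple of four. The smallest possible *b* is 2 (with *a* = 13), giving 30:28.
- *29 students is the true number*: the Data collection figure is then wrong, and the split is still 16:13.

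On every reading at least one stated feature fails, and the 1:1 ratio fails on all of them.

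**3. What the ambiguity could mean for the primary outcome**

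The article gives no SD, target difference or power for competence, so these are assumptions: a difference of 0.8 SD and a two-sided unadjusted two-sample t-test. Power is taken from the noncentral t distribution with noncentrality δ = 0.8 × √(n₁n₂/(n₁ + n₂)) and n₁ + n₂ − 2 degrees of freedom. It is shown at α = 0.05, matching the 95% interval in the Data analysis section, and at the α = 0.01 of the Sample size section.

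| Intervention v control | δ | Power, α = 0.05 | Power, α = 0.01 |
|---|---|---|---|
| 29 v 29 (58 at 1:1) | 0.8 × √14.50 = 3.05 | 84.9% | 65% |
| 32 v 26 (list used twice) | 0.8 × √14.34 = 3.03 | 84.6% | 64% |
| 16 v 13 (list used once) | 0.8 × √7.17 = 2.14 | 54.2% | 29% |
| 15 v 14 (29, near equal) | 0.8 × √7.24 = 2.15 | 54.6% | 29% |

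Without fixing an effect size, the difference detectable with 90% power at α = 0.05 is 0.87 SD for 29 v 29, 1.26 SD for 16 v 13 and 1.25 SD for 15 v 14.

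The drop follows the head count. At a fixed total, moving from near-equal to the listed ratio changes power by less than half a percentage point.

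**4. Separate check: women per student**

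Two or three women per intervention student implies:

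- 16 students: 32 to 48 women
- 29 students: 58 to 87 women

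The Sample size section plans 29 intervention women. Working back, 29/3 = 9.7 and 29/2 = 14.5, so that load corresponds to about 10 to 15 students.

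**The case against.** The block arithmetic cannot be disputed, and no other part of the article reconciles it. The objections concern how much follows from it, and several stand.

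- **The harm is conditional.** A reader might infer that the list leaves 29 students unrandomised, or that it halves the primary sample. The article supports neither. The list may have been meant for each of two semester cohorts, which would randomise all 58 with almost no loss of power. Or 58 may have been carried over from the count of women, in which case nothing is halved and the Data collection figure is simply wrong. The article does not show which.
- **The ratio matters little statistically.** A reader might blame the 2:1 blocks for the loss of power. They are not the cause, and unequal allocation does not in itself bias a randomised comparison. The ratio is a contradiction of the stated design, not a threat to power.
- **The power figures are illustrative.** They rest on an assumed effect and an unadjusted test. Competence is measured before and after, and ANCOVA is named. If baseline is a covariate, the detectable differences could be smaller.
- **The workload mismatch is a different inconsistency.** It adds no weight to the block arithmetic. With 16 students it is also a near miss (29/16 = 1.8 women each); it is large only with 29 intervention students.

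The condensed format of a journal article is no answer here. The article does not leave the scheme to another document; it states the scheme, and the parts disagree.

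**Conclusion.** The point holds as a contradiction that must be corrected. The allocation rule as written yields 29 students at 16:13, while the same plan states 58 students, blocks of four and 1:1. This rests on the article's own figures and needs no assumption.

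The consequence is that the number of students for the primary outcome is uncertain by a factor of two. How much that costs depends on which figure is right. Under the assumptions above the cost is negligible if the list is used twice, and about 31 percentage points of power at 0.8 SD and α = 0.05 (84.9% to 54.2%) if 29 is compared with the stated 58. Which number is the error cannot be settled from the article.

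The load of two or three women per intervention student is a further mismatch with the 29 intervention women, whether there are 16 or 29 intervention students.

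**What to change.** State one number of students, and give a block list that delivers it at the stated ratio:

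- for 58 students: 14 blocks of four plus one block of two, 14 × 4 + 2 = 58, split 29:29;
- for 29 students: seven blocks of four plus one student allocated at random, 7 × 4 + 1 = 29, split 14:15 or 15:14.

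If the listed blocks are what is intended, the paragraph can instead be made consistent by correcting the stated block size and ratio, and saying whether the list is used once or twice.

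The Study status section says that sampling for the quantitative phase is in process. If allocation has already begun, do not redraw the list: correct the stated number, block sizes and ratio to those actually used, and report them.

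Separately, reconcile the women per intervention student in the Intervention section with the 29 women per group in the Sample size section and the final student number.

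The cost is one corrected paragraph, one corrected student count and, if allocation has not started, a regenerated list.

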## Methods/design

### Study design

This sequential embedded mixed-methods study will include a quantitative phase and a qualitative one. A mixed (embedded) experimental design involves the collection and analysis of quantitative and qualitative data by the researcher and the integration of the information into an experimental study or intervention trial. This design adds qualitative data to an experiment or intervention to integrate the personal experience of research participants. Therefore, the qualitative data are converted into a secondary source of data embedded before and after the test. Qualitative data is added to the experiment in differrent ways, including: before the experiment, during the experiment, or after the experiment [26, 27]. Embedded mixed-methods studies that are qualitative followed by quantitative are used to understand the rationale for the results and receive feedback from participants (to confirm and support the findings of the quantitative studies) [27]. In the first stage of this study, a questionnaire for assessing midwifery students’ clinical competence will be created based on the midwifery curriculum of Iran and a review of seminal texts of midwifery. Then, the effect of continuity of care provided by midwifery students on maternal and neonatal outcomes will be assessed in a randomized clinical trial. In the third stage, a qualitative study will be carried out to investigate the perception of students and mothers. Finally, the results of the quantitative and qualitative phases will be integrated (Fig. 1).

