### Data analysis

Statistical analyses will be done using SPSS version 26.0 (SPSS, Inc., Chicago, IL, USA). The independent t-test and Chi-square tests will be used for continuous data and categorical data, respectively. ANCOVA test will be used to eliminate the influence of confounding variables. The effect size will be calculated. A 95% confidence interval (CI) and *p* values will be reported. *P*-values less than 0.5 will be considered statistically significant.

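### Only students are randomised; women's arm is set by hospital of birth, so the maternal and neonatal comparison is a non-randomised, non-concurrent comparison of two hospitals

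*Protocol article*

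**What the plan says.** The unit that is randomised is the student (Randomization): "Allocating students will be done using permuted block randomization technique with a block size of four and an allocation ratio of 1:1".

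Women are handled differently. The same section says "Mothers are randomly selected based on the hospital where they will give birth", and then fixes the result: "Razi Hospital will be the control group and Sina Hospital will be the intervention group". It describes no random draw of women, and none of which hospital receives which arm. The Intervention section says that women will be "recruited in the study using a non-probability convenience sampling method".

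Two further differences between the arms are written into the design:

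- **Period.** Under Randomization, "first the control group will provide routine care, and then the intervention group will conduct continuity of care for pregnant women".
- **Entry.** Under Intervention, "Women in the intervention group will be included in the study after their first pregnancy visit", at 6–10 weeks. Control women enter at delivery, beyond 37 weeks.

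The Study design section nevertheless says that the effect of student continuity of care "on maternal and neonatal outcomes will be assessed in a randomized clinical trial". The Abstract (Methods) and the opening of the quantitative phase say the same in substance. Under Data analysis, after t-tests and chi-square tests, "ANCOVA test will be used to eliminate the influence of confounding variables".

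**The concern.** The two descriptions of how women enter cannot both hold. A convenience sample sorted by place of birth is not a random selection, and randomising the students does not randomise the women they attend when each arm's women deliver at a different hospital.

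All the secondary outcomes are measured on women or newborns: mode of delivery, labour length, induction, bleeding, Apgar score, neonatal intensive care admission and breastfeeding. Each can plausibly differ between two hospitals because of local practice or case mix, whether or not a continuity programme exists. A difference between Razi and Sina would be reported as the effect of the programme, with the authority of a randomised trial.

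This comparison is not incidental. Pregnancy outcomes are the second specific objective, the Background makes unnecessary caesarean section a main motive for the study, and the sample size is expressed in women and derived from two proportions.

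**Working it through.** **1. Can hospital be separated from treatment?**

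Inputs: two hospitals (Data collection) and one hospital per arm (Randomization).

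Let A = 1 for a woman in the intervention arm and H = 1 for a woman delivering at Sina. Under the stated rule, H = A for every woman. A model with both terms reduces to

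E[Y] = b0 + b1·A + b2·H = b0 + (b1 + b2)·A.

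Only the sum b1 + b2 can be estimated. Between-hospital degrees of freedom for error are 2 hospitals − 2 arms = 0. Drawing the hospital labels by lot would not change this.

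**2. Do period and entry point add to it?**

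The control phase precedes the intervention phase, so a period indicator also equals A. So does an entry indicator (early pregnancy against delivery). The unadjusted difference between arms therefore estimates

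programme + hospital + period + entry point.

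The entry rule has a direct consequence: every control woman has already passed 37 weeks when she is enrolled, while an intervention woman enrolled at 6–10 weeks need not reach that point.

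**3. What can ANCOVA remove?**

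The Instruments section records age, parity, BMI and obstetric history. Adjusting for these can remove the part of the hospital term that reflects measured case mix. Hospital policy, staffing, thresholds for intervention and calendar change remain tied to A.

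**4. How much could it matter?**

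The plan's group size: 23 / (1 − 0.20) = 28.75, rounded up to 29 per group, 58 women, as stated under Sample size. (How the 23 was reached is a separate matter.)

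The documents give no caesarean rate for either hospital, so the rates below are assumptions chosen to show the mechanism. Setting: 29 women per arm, no programme effect, and an uncorrected Pearson chi-square test at two-sided 0.05, the level that matches the planned 95% confidence interval. (The threshold printed under Data analysis is 0.5, also a separate matter.)

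The rejection probability is the sum, over all pairs (x, y) with chi-square above 3.84, of Bin(x; 29, p_a) × Bin(y; 29, p_b), where

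chi-square = 58·[x(29 − y) − y(29 − x)]² / [29·29·(x + y)·(58 − x − y)].

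| Assumed caesarean rates in the two hospitals | Gap | Probability of a significant result with a programme that does nothing |
|---|---|---|
| 50% v 50% | 0 points | 4.8% |
| 45% v 55% | 10 points | 11.5% |
| 40% v 60% | 20 points | 32.8% |
| 35% v 65% | 30 points | 63.4% |

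More women at the same two hospitals would not help. The bias stays the same while the standard error shrinks, so the false-positive rate rises.

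**The case against.** Five points can be made for the plan.

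- **The primary outcome is on students, and students are randomised.** This stands. A reader might infer that the trial as a whole is not randomised; the documents do not support that, because they describe a permuted-block allocation of students. The primary comparison is not wholly insulated, though: if students attend the women of their own arm, as described, the arms also differ in hospital and period.
- **Eligibility is narrow and case mix is recorded.** Women must be low-risk with singleton pregnancies and no previous caesarean. This stands in part. It would be too strong to say that any analysis carries the entire hospital difference; that is true only of the unadjusted comparison.
- **The plan never says that ANCOVA is meant for hospital.** This stands. It may be intended for student competence, which has a baseline measurement. A reader might take the sentence as a claim to remove the hospital effect; the text is general and does not say so. It is still too broad as worded, because no ANCOVA could do that here.
- **The caesarean rates are invented.** They are assumptions and do not estimate the bias in this trial. The aliasing in steps 1 and 2 does not depend on them.
- **An article condenses the full protocol.** This does not help. The allocation rule is stated, not omitted, and no later analysis plan could separate two identical indicators.

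One more inference should be resisted: that stratifying students by hospital would justify the randomised label for maternal outcomes. Women would still be a convenience sample, with period and entry point tied to arm.

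**Conclusion.** The point holds for every maternal and neonatal outcome. As written, the plan calls this comparison randomised, but its own allocation rule makes hospital, calendar period and entry point coincide with arm. That conclusion is structural and needs no numerical assumption.

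The size of the bias cannot be known from the documents. Under the assumed caesarean rates, a between-hospital gap of 10 to 30 points raises the false-positive rate from 4.8% to between 11.5% and 63%. Those figures apply to an unadjusted test with 29 women per arm and count the hospital gap only; period and entry-point effects could add to it or offset it. This must be corrected, because it changes what the trial can conclude on its second objective.

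**What to change.** **Needed in any case.**

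- In the Abstract (Methods), Study design, the opening of the quantitative phase, and Randomization, drop the terms randomized and randomly selected where they refer to women or to maternal and neonatal outcomes. Describe that objective as a non-randomised, non-concurrent comparison of two hospitals.
- Under Data analysis, say that ANCOVA adjusts only for measured covariates and cannot remove hospital or period effects.
- Limit causal conclusions on these outcomes accordingly.

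The cost is wording and a weaker claim.

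**Also, if enrolment still allows.** Stratify the student randomisation by hospital so that both arms attend women at both hospitals, and adjust the analysis for hospital. Both hospitals are already in the study, so the cost is re-rostering students. Study status reports that sampling for the quantitative phase is already in process, so some women may have been enrolled under the present rule and it may be too late. This step removes the hospital aliasing only. It does not randomise women or remove the period and entry-point differences, so the relabelling is needed either way.

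**For the primary outcome.** Keep the description of students as randomised, and add that the arms also differ in hospital and period.

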### Intervention

Women who meet the inclusion criteria will be recruited in the study using a non-probability convenience sampling method. Women in the intervention group will be included in the study after their first pregnancy visit (6–10 weeks of gestation) and will receive continuous care by midwifery students. Women in the control group will receive the usual and routine care, and will be included in the study at the time of delivery. They will have a gestational age of more than 37 weeks based on the inclusion criteria of the study. Their delivery will be performed by midwifery students who will follow them up until six weeks after delivery.

At first, the necessary training will be given by the lead researcher (FR) to the students in orientation sessions held for both groups separately. In the intervention group, each midwifery student as the main midwife will be responsible for taking care of two or three pregnant women and will be the back-up midwife for two other pregnant women (under the supervision of other students). The lead researcher will create a group in WhatsApp with the participation of students in the intervention group, and they can communicate with each other and the researcher. Also, the midwifery students will be directly and indirectly under the supervision of a qualified person (lead researcher). Another WhatsApp group will be created for the women of the intervention and control groups (to facilitate communication between the researcher and the women). Two midwifery students will be introduced to each pregnant woman in the intervention group (as a main midwife and a backup midwife). If the main midwife is not available, the woman will be in contact with the backup midwife. The backup student will meet the woman at least once and will be introduced to her.

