### Follow-up

The students in the intervention group will start prenatal care < 20 weeks of gestation. At least five round of prenatal care will be provided by each student according to national guidelines for each pregnant woman. Pregnant women can communicate with their in-charge students in non-emergency cases from 8:00 a.m. to 23:00 p.m. and in emergency cases 24 h a day, all days a week. All reports will be recorded by the students. During labor and delivery, the student and the lead researcher will be present at the mother's bedside. In case of natural vaginal delivery (NVD), delivery will be done by a student midwife under the supervision of the researcher. In case of cesarean delivery (CS), a student will be present at the patient's bedside. Postpartum care will be provided by midwifery students in both groups (intervention and control). Each student will be at the mother's bedside for two hours after delivery. The conditions of labor, delivery, and the neonate will be recorded by the student in the relevant form. Also, the mother will be followed up by telephone for up to 6 weeks after delivery (postpartum). The clinical competency questionnaire will be completed by students before and after the intervention.

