### Inclusion criteria

Inclusion criteria for midwifery students will be: studying at the seventh and eighth semester and willingness to participate in the study.

Inclusion criteria for service recipients (pregnant women) will be: age 18 – 40 years, Iranian nationality, singleton pregnancy, low risk pregnancy, and gestational age < 20 wks.

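### Intervention women enter after an early first visit and control women at delivery, with no workable booking condition for controls, so the arms may differ in booking time

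*Protocol article*

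**What the plan says.** All references are to the second stage (the randomised trial) of the protocol article.

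- **Intervention, intervention arm:** "Women in the intervention group will be included in the study after their first pregnancy visit (6–10 weeks of gestation", and they then receive continuous care from students.
- **Intervention, control arm:** "Women in the control group will receive the usual and routine care, and will be included in the study at the time of delivery". The next sentence adds: "They will have a gestational age of more than 37 weeks based on the inclusion criteria of the study".
- **Inclusion criteria:** for pregnant women in general, with no version by arm, the list ends with "singleton pregnancy, low risk pregnancy, and gestational age < 20 wks".
- **Follow-up:** "The students in the intervention group will start prenatal care < 20 weeks of gestation". At least five antenatal rounds by the student follow.
- **Data collection:** the students are described as "providing care to 58 pregnant women in six health centers and two hospitals". The health centers are not linked to an arm.
- **Randomization and Intervention:** students are randomised. Women are a convenience sample, and their arm follows from the hospital of birth (Razi control, Sina intervention). The control period runs first.

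**The concern.** When a woman first comes for antenatal care is settled before the programme can act on her. If one arm is restricted on that feature and the other is not, any outcome related to it can differ between arms with no effect of continuity of care.

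The outcomes exposed are those measured in women and newborns under Secondary outcome, such as mode of delivery, induction, neonatal intensive care admission and breastfeeding. They are secondary, but the effect on pregnancy outcomes is one of the three specific objectives, and the sample size is expressed in women. A difference caused by booking time would be read as an effect of the programme.

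**Working it through.** There is no figure in the plan to reproduce on this point, so the check sets the sections side by side and adds a scale illustration on assumed inputs.

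**1. Can the shared criterion be met at control entry?** Controls enter at more than 37 weeks; the criterion is below 20 weeks. Read as gestation at entry, a control woman exceeds the limit by more than 37 − 20 = 17 weeks, so none qualifies. The Intervention section nevertheless attributes the 37-week condition to the inclusion criteria, which contain no such item.

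**2. What do the possible readings imply?** The intervention window is 6–10 weeks or below 20 weeks, depending on the section. For controls, the 20-week criterion is either inoperative or means in care before 20 weeks.

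| Intervention window | Control condition | Booking condition the same in both arms? |
|---|---|---|
| 6–10 weeks | none workable | No |
| 6–10 weeks | in care before 20 weeks | No: controls may have booked after week 10 |
| below 20 weeks | none workable | No: only controls can include bookings at 20 weeks or later |
| below 20 weeks | in care before 20 weeks | Yes |

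Only the last row aligns the arms. It needs one particular resolution of the intervention window and a control condition that the article does not state.

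**3. Does randomisation repair it?** No. It applies to students. Women are recruited by convenience and assigned by hospital.

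**4. Does adjustment repair it?** Not as shown. Data analysis names ANCOVA without covariates. The items listed under Instruments include gestational age and last menstrual period but not gestation at first visit. The full form may hold it, so this is no finding by itself; it means only that the article gives no assurance of adjustment.

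**5. Scale, on assumed inputs only.** Let *s* be the share of controls who would not meet the intervention arm's booking condition, and *d* the difference in outcome risk between them and women who would. If the remaining controls have the intervention arm's risk *r* and there is no treatment effect, the control risk is (1 − *s*)*r* + *s*(*r* + *d*) = *r* + *sd*. The spurious difference is therefore *s* × *d*.

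| *s* | *d* = 10 points | *d* = 20 points | *d* = 30 points |
|---|---|---|---|
| 10% | 1 | 2 | 3 |
| 30% | 3 | 6 | 9 |
| 50% | 5 | 10 | 15 |

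Neither *s* nor *d* comes from the document.

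**The case against.** Five counter-arguments deserve an answer.

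- **Controls are not unselected.** A reader might infer that the control arm takes anyone who arrives at term. The article does not support that. Age, nationality, singleton and low-risk criteria are written for all women, and the exclusions (among them previous caesarean section, alcohol and tobacco use, and disease needing specialist care) carry no restriction by arm. Several of these bear on mode of delivery and neonatal outcome. This stands, but none of them concerns booking time: a low-risk woman at term may have booked late.
- **The 20-week criterion may mean in care before 20 weeks.** That is possible, and would narrow the gap or, in one reading above, close it. The article does not say so, and its 37-week sentence points elsewhere.
- **A difference in care sector is not documented.** A reader might infer that controls used other providers, such as private ones. The Background describes antenatal services as given in public health centers, and nothing says controls went elsewhere. What stands is that their setting is unspecified.
- **Regular attendance is partly the programme.** The five or more rounds are delivered by the students, so a difference in visits after entry cannot be counted as selection. Only booking time before entry can be.
- **Precision and larger problems dominate.** With 29 women per arm and an assumed risk of 0.5, the standard error of a difference is √(2 × 0.25/29) = 0.131, about 13 points, and the planning contrast of 0.51 against 0.021 is 48.9 points. Most of the illustrated biases are smaller than that standard error. This is fair as to scale, but a systematic shift is not covered by the confidence interval. Assignment by hospital and period is a separate problem; the booking asymmetry would persist even with identical hospitals.

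**Conclusion.** The concern holds in limited form. The arms are entered at different points in pregnancy under gestational conditions that conflict across Intervention, Follow-up and Inclusion criteria, and no workable booking condition is stated for controls. The arms may therefore differ in booking time, and the controls' antenatal setting is left open.

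The consequence is possible bias in the secondary maternal and neonatal outcomes. A reader might extend this to the whole trial. That goes too far, because the primary outcome is measured in randomised students and is not biased through this route.

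The size cannot be computed from the document. The 1 to 15 points above assume a share of 10–50% and a risk difference of 10–30 points, and the conclusion does not depend on them. It rests on the text being followed as printed. If the full protocol already defines the 20-week criterion as time of booking for both arms and uses a single window, the point reduces to correcting the wording.

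**What to change.** 1. Reconcile Intervention, Follow-up and Inclusion criteria to one gestational window for the first antenatal visit. Which window to use is for the investigators to decide.
2. Apply that window to both arms. For controls, word it as gestation at first visit and check it from the antenatal record at admission; state the gestation at delivery as a separate condition.
3. Require antenatal care at one of the six study health centers in both arms.
4. The Study status section says sampling is under way. For controls already enrolled, extract first-visit gestation and center from the record and report both by arm.

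The cost is a change of criterion wording, a record check for each control and somewhat slower control recruitment. The change removes the difference in booking condition only. It does not remove confounding by hospital and by period, which needs its own answer.
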